#### Criteria for discontinuing or modifying allocated interventions {11b}

Owing to the nature of the intervention, being a surgical technique and use of specific implant, and the timing following randomisation, it is not anticipated that any participants will be discontinued from allocated intervention following randomisation. If a participant suffers graft failure or contralateral ACL knee rupture, then analysis via GNRB assessment may be changed. Participants may withdraw from the study without citing a reason, but reasons may include the participant has chosen to withdraw, postoperative graft rupture or failure or the participant has experienced an adverse event. If a patient indicates that they wish to withdraw, this will be recorded in the REDCap project, and they will not be asked to complete any further research-only assessments. They will be reassured that they will continue to receive care and any subsequent management at Western Health. If a patient withdraws from the study, data collected to this point will remain within the study for analysis unless the participant specifically requests otherwise.

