#### Secondary outcomes

Secondary outcomes are fourfold and will include (i) PROMs, (ii) return to sport rates, (iii) complications and (iv) examination findings.i)PROMs will be recorded preoperatively and post-operatively at 6 weeks, 3 months, 12 months and 24 months. PROMs collected will include the following:EQ5D-5L: The EuroQol EQ-5D-5L is a validated, generic, self-reported outcome measure covering five health domains that are used to facilitate the calculation of quality-adjusted life years (QALYs) in health economic evaluations. The original EQ-5D questionnaire contained three response options within each of five health domains (mobility, self-care, usual activities, pain/discomfort and anxiety/depression) [33]. More recently, the EQ-5D-5 L has been developed to overcome problems with ceiling effects and to improve sensitivity [43]. The 5 L version consists of the same five domains as the original but with five response options.The International Knee Documentation Committee (IKDC) score: The IKDC is a knee-specific patient outcome questionnaire often used after ACL reconstruction [31]. It is a subjective tool that provides an overall patient score (0–100), often interpreted as a measure of function, where higher scores represent a greater function. It aims to address three categories: symptoms, activity and overall function, and has shown adequate test-retest reliability and good construct validity in patients with issues at the knee [44].Knee injury and Osteoarthritis Outcome Score Quality of Life sub-scale (KOOS-QOL): This subscale is a 4-item questionnaire designed to evaluate the knee-specific quality of life, has been utilised among ACL surgical trials [30] and has been established to have validity, responsiveness and reliability in patients undergoing ACLR [45].ACL return to sport index (ACL-RSI): Psychological readiness to return to sport will be evaluated with the ACL-RSI. It is a 12-point questionnaire validated to evaluate a patient’s confidence and readiness to return to sport [34] and exhibits high internal validity and structural consistency [46]. Given the theoretical increased stability offered by suture tape augmentation, particularly in the early rehabilitative period, it follows that patients treated with this may experience improved perception of knee function and subsequent confidence in rehabilitation and sporting activity across the early postoperative period.Self-reported pain: We will record postoperative pain levels and long-term knee pain scores utilising 10-point visual analogue scale pain scores (VAS) where 0 is no pain and 10 is the worst pain imaginable.ii)Complications:We will record complications and adverse events including wound complications, infection rates, return to surgery, e.g. meniscal tears, graft failure, contralateral knee ACL rupture, residual effusion, rates of symptomatic arthrofibrosis of the knee and second look arthroscopy findings and the rates of sterile effusion. These will be recorded upon review of each patient’s medical record at 2 years.iii)Return to sport and activity:Return to sport and activity will be assessed via a self-reported questionnaire delivered concomitantly with PROMs preoperatively and post-operatively at 6 weeks, 3 months, 12 months and 24 months. Return to activity will be evaluated through the Marx activity scale, a four-item activity rating scale which has been shown to have excellent retest reliability in patients with knee injuries [32]. Participants will be asked to record on a scale of 0–4 how often they are able to perform each of running, cutting, deceleration and pivoting in their most active state across the preceding 12 months. A maximum score is 16 points. Participants will also be asked about their dichotomous return to sport status, their expectations regarding timing of return to sport, return to preinjury level of sport and the time postoperatively to return to sporting activity. These questions, along with the full set of pre-operative and post-operative PROMS, are included in Additional file 1.iv)Examination findingsExamination findings will be taken preoperatively at examination under anaesthesia and post-operatively at 6 weeks, 3 months and 12 months. Examination findings including the range of motion (ROM), the presence of knee effusion, Lachmans, pivot shift and anterior drawer testing will be recorded. All assessments will be undertaken by lead surgeons S.T, L.B.

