### Plans to promote participant retention and complete follow-up {18b}

PROMs and return to sport data will be collected by online survey, deliverable by email or text message with the aims to increase follow-up rates among a technologically inclined patient cohort. All follow-up examinations and GNRB assessments will be performed concurrently with follow-up surgical appointments until the 12-month mark in order to reduce the study burden on the individual. If a participant withdraws from the study, or suffers graft failure, no further data will be collected; however, data collected up until this point will be included in the study and absent data will be analyzed according to intention to treat principles.

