### Methods in analysis to handle protocol non-adherence and any statistical methods to handle missing data {20c}

All principal analyses will be based on the intention-to-treat principle, analysing participants in the groups to which they are randomised. Missing data will be quantified and if possible multiple imputation will be used; otherwise, simple imputation will be used. Owing to the nature of enrolment and randomisation in this study, it is unlikely that a participant will be randomised and subsequently not receive the intervention, and thus adherence does not apply directly to the intervention arm.

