### Adverse event reporting and harms {22}

Participant safety will be ensured via standard institutional protocols. The use of the GNRB is established to be safe in pre-operative [53] and early post-operative patients [42], with no adverse events reported, and this will be expressed verbally to patients prior to participation. Adverse events are defined as medical occurrences that may or may not have a causal relationship with the surgical treatment administered. Any adverse events identified will be recorded and reviewed regularly by the Internal Trial Monitoring Committee. The Principal Investigator will determine causality. The number and type of adverse events (AEs) will be recorded up to 24 months. Any AEs will be noted on the REDCap database. These events will also be reviewed by the participants’ medical and surgical teams (who are not a part of the investigative team) as part of standard care.

Serious adverse events (SAE) are defined as any untoward and unexpected medical occurrence that results in death, is life-threatening, requires hospitalisation or prolongation of existing inpatients’ hospitalisation, results in persistent or significant disability or incapacity, is a congenital anomaly or birth defect, or is any other important medical condition which, although not included in the above, may require medical or surgical intervention to prevent one of the outcomes listed. All SAEs will be reported to the approving ethics board within 72 h of the investigators becoming aware of them. SAEs that may be expected as part of the surgical interventions and that do not need to be reported to the HREC are complications of anaesthesia or surgery (wound infection, bleeding or damage to adjacent structures such as nerves, tendons and blood vessels, delayed wound healing, and thromboembolic events, femoral or tibial fracture).

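### Section {18b} ends all data collection at withdrawal or graft failure, which cannot be squared with the narrower withdrawal rule in {11b} or with the planned 2-year complication review and 24-month adverse event recording

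*Protocol article*

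**What the plan says.** Four parts of the protocol article bear on what happens to data after a participant leaves.

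- **Retention, {18b}:** "If a participant withdraws from the study, or suffers graft failure, no further data will be collected". Data gathered before that point are to be included in the study, without qualification.
- **Discontinuation, {11b}:** after withdrawal "they will not be asked to complete any further research-only assessments", and patients are told that "they will continue to receive care and any subsequent management at Western Health". Possible reasons for withdrawing include "postoperative graft rupture or failure or the participant has experienced an adverse event". On data already held, "data collected to this point will remain within the study for analysis unless the participant specifically requests otherwise".
- **Secondary outcomes, complications:** the list includes infection, return to surgery, graft failure, residual and sterile effusion, arthrofibrosis and second-look arthroscopy findings. "These will be recorded upon review of each patient’s medical record at 2 years".
- **Adverse events, {22}:** "The number and type of adverse events (AEs) will be recorded up to 24 months".

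The analysis rule in {20c} is: "All principal analyses will be based on the intention-to-treat principle, analysing participants in the groups to which they are randomised".

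**The concern.** The scope of withdrawal matters more here than in most trials. Sections {11c} and {13} explain that nearly all follow-up coincides with routine surgical care and that only the 2-year GNRB visit lies outside it. A rule that stops research-only contact therefore removes little beyond the surveys and that visit. A rule that stops all data also removes the findings from later routine clinic reviews and, above all, the 2-year record review.

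The record review is the source of the complication outcomes and needs nothing from the patient. Because an adverse event is among the possible reasons for leaving, the lost follow-up may be related to the outcome being counted. The Discussion puts forward a secondary hypothesis of equivalent complication profiles and names sterile effusion as an objection that sceptics may raise. Incomplete counting of later complications would weaken the evidence on that hypothesis.

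The same sentence in {18b} also ends collection at graft failure. Graft failure is a study outcome, not a decision to leave. Return to surgery and second-look findings, both listed complications, may well come after it.

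**Working it through.** The protocol gives no figure for this point, so the check is mainly a comparison of text.

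**Step 1. What each section implies for a patient who withdraws at, say, 4 months.**

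| Item | {18b} read literally | Other sections |
|---|---|---|
| Surveys, 24-month GNRB visit | stop | stop ({11b}) |
| Findings at the 12-month routine review | stop | not plainly stopped ({11b}) |
| 2-year record review for complications | not done | done for each patient (secondary outcomes) |
| Adverse events after month 4 | not recorded | recorded to 24 months ({22}) |
| Data gathered before month 4 | included | included unless the participant asks otherwise ({11b}) |

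Staff cannot obey {18b} as written and also carry out the record review for every patient and adverse event recording to 24 months. That conflict is firm. The difference from {11b} is one of scope.

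**Step 2. Is the lost information obtainable?** Yes, in principle. Under {11b} care continues at the same institution, so its records keep accruing, and the review at 2 years is already planned.

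**Step 3. What exactly is lost?** Only events after withdrawal. An event that prompted the withdrawal and was recorded beforehand is retained, unless the participant asks for removal.

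**Step 4. Can the loss be sized?** Not from the documents. Section {14} expects 30% dropout among 66 patients: 0.30 × 66 = 19.8, about 20. It attributes this to loss to follow-up, contralateral rupture and graft failure and does not list withdrawal, so 20 is only a rough ceiling. To show how wide the possibilities are, let *w* be the number withdrawn and *r* the chance of a later complication in each. Both are assumptions.

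- Expected missed events = *w* × *r*
- Chance of missing at least one = 1 − (1 − *r*)^*w*

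| *w* | *r* | Expected missed | Chance of at least one |
|---|---|---|---|
| 2 | 0.05 | 0.1 | 1 − 0.95² = 10% |
| 5 | 0.10 | 0.5 | 1 − 0.90⁵ = 41% |
| 10 | 0.10 | 1.0 | 1 − 0.90¹⁰ = 65% |
| 20 | 0.20 | 4.0 | 1 − 0.80²⁰ = 99% |

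The range, 0.1 to 4 missed events, is too wide to serve as an estimate. It also says nothing about how the missed events would divide between arms.

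**Step 5. Primary outcome.** The 24-month GNRB visit is the one attendance outside routine care, so withdrawal ends it under either rule. Reconciling the sections changes little there.

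**The case against.** The strongest reply is that {11b} and {18b} do not truly conflict. Section {11b} says only what patients will not be asked to do, and that earlier data remain. It never says that record data will go on being collected, and its wording is compatible with collection stopping. This stands: a reader might infer a flat contradiction between the two, but the text supports only a difference of scope. It does not rescue {18b} against the record review and section {22}, which cover every patient to 2 years.

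Second, using records after withdrawal depends on the consent given, and neither the consent form nor the full protocol is shown. This also stands. It is why the remedy must let a participant refuse record access.

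Third, a reader might infer that complications will be understated in the tape arm and the comparison pulled toward no difference. The documents do not support that. They say an adverse event may be a reason to withdraw, not that withdrawals cluster among patients with problems or in one arm. Participants are blinded to allocation. Any worked example that puts the missed events in one arm would be invented. Nor should every listed complication be called a suspected harm of the tape: the Discussion names stress shielding and synovial complications such as sterile effusion.

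Fourth, a reader might infer that the participant's option in {11b} to have earlier data removed must go, because it could take a randomised patient out of the intention-to-treat set. That option can be read as an exception to the general rule in {18b}, and keeping it is a consent question on which reasonable reviewers differ. The two sections should agree; the option need not be deleted.

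**Conclusion.** The point holds as an inconsistency that should be reconciled. Section {18b} is broader than {11b} and cannot be followed together with the 2-year record review and the 24-month adverse event window. Followed literally, it loses later complications in withdrawn patients, and those after graft failure, although they could be read from a record that is to be reviewed anyway.

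What is at stake is the secondary complication comparison. It could be biased if withdrawals related to complications differ by arm; neither the size nor the direction can be estimated from the documents. The primary GNRB result is largely unaffected, and events recorded before withdrawal are normally kept. The conclusion assumes that staff would apply {18b} as written and that at least some withdrawing patients would leave consent to record use in place. The case for acting rests on the clear textual conflict and the low cost of removing it, not on a demonstrated large bias.

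**What to change.** Reword {18b} to agree with {11b}, the complications paragraph and {22}:

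1. Withdrawal stops research-only contact, namely the surveys and the 24-month GNRB visit. Findings from routine visits, and the 2-year record review for complications and adverse events, continue unless the participant separately refuses record access.
2. Record the level of withdrawal in REDCap: research contact only, or record access as well.
3. Take graft failure out of the sentence as a trigger for ending complication and adverse event collection. How GNRB data are handled after graft failure can be dealt with separately.
4. State one rule, in both sections, for data already collected. The participant's option to request otherwise may stay; if so, {18b} should mention it.

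The cost is protocol wording, ethics approval of that wording and of any matching consent text, and one database field. No visits or staff are added, since record review is already planned for each patient. Some participants may still refuse record access, so some loss will remain, but it will then be documented.

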### Sample size {14}

All statistical methods and power analysis were developed through consultation with an independent statistician. Power analysis was performed with G*power 3.1 Software. To achieve a minimum 80% statistical power with an alpha value of 0.05, power analysis based on a hypothesised mean residual side-to-side difference of 2 mm of anteroposterior tibial translation yielded a sample size of *n*=48 (24 per group) utilising an expected independent *t*-test [47–50]. Although previously published KT-1000 data was utilised for power analysis, it has been shown that the GNRB exhibits similar absolute measures in side-to-side anterior tibial translation to KT-1000 utilised by experienced observers, whilst having reduced scatter around the mean [38]. This would mean that utilising KT-1000 published data to establish a power analysis would be a conservative method, and likely over-estimate the required sample size to detect significant differences.

Secondary power analysis based on 2-year IKDC total scores yielded a total sample size of 48 (*n*=24 in each group) to detect significant differences with 80% power and an alpha value of 0.05 with an anticipated independent sample two-tailed *t*-test. This is based on a previous retrospective study of suture-tape ACL reconstruction which reported a mean change from baseline IKDC of 56 ± 17 in SA-augmented ACLR, compared with 38 ± 25 in conventional ACLR [29, 51]. Secondly, previous studies evaluating the IKDC [51] which reported that a change score of 12.8 points would be sufficient to detect differences between those who have and have not had improved knee outcomes. Power analysis yielded a sample size of 48. Dropout rates are expected to be 30% based on institutional experience, owing to loss to follow-up and contralateral ACL rupture and graft failure, and as such 66 patients will be recruited. This is expected to take approximately 1–2 years of recruitment based on historical institutional caseloads.

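### Data collection stops at graft failure, so post-failure patient-reported and return-to-sport data are never obtained, and 24-month values must be imputed with no failed knees to inform them

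*Protocol article*

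**What the plan says.** Four sections of the protocol article bear on what happens after the study graft fails.

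- Retention {18b}: "If a participant withdraws from the study, or suffers graft failure, no further data will be collected". It continues that "data collected up until this point will be included in the study and absent data will be analyzed according to intention to treat principles".
- Sample size {14}: "Dropout rates are expected to be 30% based on institutional experience, owing to loss to follow-up and contralateral ACL rupture and graft failure". Failure is therefore budgeted as loss.
- Missing data {20c}: "Missing data will be quantified and if possible multiple imputation will be used; otherwise, simple imputation will be used". No separate rule is given for values missing because the graft failed. The same section says "All principal analyses will be based on the intention-to-treat principle, analysing participants in the groups to which they are randomised".
- Discontinuation {11b}: "If a participant suffers graft failure or contralateral ACL knee rupture, then analysis via GNRB assessment may be changed". What the change would be is not stated.

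Three other places matter. Graft failure is itself a secondary outcome (Background {6a}, Secondary objectives, Outcomes {12}). Outcomes {12} takes complications from a review of each patient's medical record at 2 years. Adverse event reporting {22} records adverse events up to 24 months.

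**The concern.** Graft failure is not an ordinary loss to follow-up. It is a result of treatment, it lies at the far end of the laxity scale, and the Discussion presents protection of at-risk grafts as part of the tape's purpose. Stopping collection at that event makes missingness depend on outcome, and possibly on arm.

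An imputation model can learn only from observed data. Under {18b} no failed graft in either arm contributes a laxity, questionnaire or return-to-sport value after failure. Readings from before the failure, where they exist, describe a graft that was still holding. A later analysis plan can choose the imputation model but cannot recover data that were never collected.

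At stake are the 24-month laxity, patient-reported and return-to-sport comparisons. If tape prevents failures, these comparisons may understate its benefit. If tape causes failures, they may overstate it. Nothing practical forces the surveys to stop: they go out by automated email and are completed online.

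**Working it through.** **Sample size figures used for scale**

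- The evaluable number of 48 reproduces from the IKDC inputs. The pooled SD is √((17² + 25²)/2) = 21.38, d = 18/21.38 = 0.842, and a two-sided t-test at 80% power needs 23.1, so 24 per group.
- For the primary outcome no SD is given. With 24 per group and 80% power, d = 0.826, so 2 mm implies an SD of 2/0.826 ≈ 2.42 mm. This SD is inferred, not stated.
- 66 randomised 1:1 gives 33 per arm. Whether 66 follows from 48 and 30% is a separate question and is not needed here.

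**Bias in the laxity difference**

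Let m be an arm's mean side-to-side laxity had every graft held, p its failure rate and g the excess laxity of a failed knee.

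- Mean over all randomised in an arm: m + p × g.
- Control minus tape over all randomised: (m_control − m_tape) + (p_control − p_tape) × g.
- If failed knees receive values like those of intact knees, only the first bracket is estimated.
- Part lost: (p_control − p_tape) × g.

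The documents give neither p nor g. All rates below, and g = 4 mm, are assumptions.

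| Failure, control vs tape | Calculation | Part lost | Share of 2 mm |
|---|---|---|---|
| equal rates | 0 × 4 | 0 mm | 0% |
| 3-point gap | 0.03 × 4 | 0.12 mm | 6% |
| 5-point gap | 0.05 × 4 | 0.20 mm | 10% |
| 12% vs 3% | 0.09 × 4 | 0.36 mm | 18% |
| 5% vs 10% | −0.05 × 4 | −0.20 mm | 10%, flattering tape |

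With g from 3 to 8 mm, the 12% versus 3% row runs from 0.27 to 0.72 mm and the 5% versus 10% row from −0.15 to −0.40 mm.

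**How extreme is 12% versus 3%?** In 33 per arm it means about 4 failures against 1 (33 × 0.12 = 4.0; 33 × 0.03 = 1.0). The Discussion cites 1290 patients as needed to power for graft failure. Assuming 80% power, two-sided 0.05 and equal arms, 12% versus 3% would need only about 261. For control rates of 5 to 12%, a total of 1290 corresponds to a gap of about 2.9 to 4.6 points, or 0.12 to 0.18 mm at 4 mm. The 3 to 5 point rows are therefore the more plausible ones.

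**Against sampling error:** the standard error of the difference with 33 per arm is 2.42 × √(2/33) ≈ 0.60 mm.

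**IKDC:** if failed patients score 20 to 30 points lower (assumed), a 3 to 5 point gap hides 0.03 × 20 = 0.6 to 0.05 × 30 = 1.5 points, and 12% versus 3% hides 1.8 to 2.7. The design figures are 12.8 and 18 points.

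**Complications:** set side by side, {18b} ends all collection at failure, {12} reviews every patient's record at 2 years, and {22} records adverse events to 24 months. These cannot all be followed for a patient whose graft fails at, say, 10 months.

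**The case against.** A reader might infer that the worst outcomes leave every comparison, complications included, and that tape would get no credit for preventing failures. The documents do not support that. Graft failure is a listed secondary outcome, complication rates are compared between arms with Fisher's exact test, and record review and adverse-event recording both extend to 2 years. Failures are counted by arm. For complications after the failure, all that remains is a conflict between sections.

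A reader might also infer that the plan breaks intention to treat outright. In the sense that {20c} gives the term, it does not: failed patients stay in their allocated arm with their earlier data. What is lost is their real later data.

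It is also fair to say that {20c} names no imputation model, that 3- and 12-month arthrometer readings may be available for some failed patients, and that {11b} leaves arthrometer handling open. So it is not established that failed knees would be imputed exactly as if intact. The arithmetic above is conditional on that. What stands is that no model would have post-failure observations to learn from.

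For laxity, stopping is partly defensible. The primary objective concerns laxity after a primary hamstring graft, and after a revision the arthrometer measures a different graft. No reading at the time of failure is scheduled, so one cannot be assumed. Forcing failed knees into the primary mean would also cost precision: with 10% failing in both arms at 4 mm, the SD rises from 2.42 to √(2.42² + 0.1 × 0.9 × 4²) = 2.70, and the required number by about 25%. This argues against changing the primary comparison. It does not argue for stopping the questionnaires.

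**Conclusion.** The concern holds for patient-reported outcomes, return to sport and the handling of laxity after failure. Collection stops because of a treatment outcome, the patient is budgeted as dropout, and the missing values are imputed under a general rule. The loss is permanent and avoidable.

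The likely size is modest: about 0.1 to 0.2 mm for plausible gaps in failure rate, 0 if the arms fail equally, and 0.36 mm in an extreme case, against 2 mm. These figures rest on assumed failure rates, an assumed 4 mm excess and imputed values resembling intact knees. The direction cannot be known in advance. The figures do not show that the primary conclusion would be overturned.

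This should be fixed. It is a flaw in data collection with a cheap remedy, and it does not invalidate the design.

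**What to change.** 1. In {18b}, delete the words that put graft failure alongside withdrawal. Continue the online patient-reported and return-to-sport surveys to 24 months after failure unless the patient withdraws, and analyse them by allocated arm.
2. Reconcile {18b} with {12} and {22}, so that complications and adverse events after a failure are recorded to 24 months.
3. In {14}, remove graft failure from the causes of dropout for the patient-reported outcomes. Its share of the 30% is not given, so the sponsor must supply it.
4. In {11b}, replace the open wording on arthrometer analysis after graft failure with one rule fixed before unblinding. Keep the planned 24-month comparison as primary, state that it does not reflect post-failure laxity where values are imputed, and add a supportive rank analysis that places every graft failure worst. Contralateral rupture, named in the same sentence, is a different problem because the reference knee is affected. Its handling needs its own statement.

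Cost: protocol wording, a few extra automated surveys, one more analysis, and somewhat more variable patient-reported estimates because poor outcomes are kept in.
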